### Data management

After review by the investigators and inspectors, completed CRFs will be sent to a specified statistics center, where data entry and management will be completed by two independent data administrators to ensure data accuracy. All data will be managed by DAS (Direct Attached Storage) for electronic data management system. To confirm the database, the principal investigator, the sponsor and statisticians will perform a blind review, and make a statistical analysis plan. Finally, the data will be locked and analyzed in accordance with the statistical analysis plan.

### Sample size calculation

Based on a previous clinical study [20], the mean duration of all symptoms for the common cold was estimated to be 7 days with a standard deviation of 3 days. Reduction in the duration of all symptoms by 2 days is supposed to be clinically relevant. Using Package for Encyclopedia Medical Statistics (PEMS) 3.2 with 90% power and α = 0.05 (2-sided), the sample size needs to be 48 cases for each group. Considering a drop-out of 20%, 60 subjects should be recruited in each group. Consequently, the total sample size is determined to be 240 patients.

### Statistical analysis

The data analysis will be performed by professional statisticians, in accordance with the statistical analysis plan for this trial. The full analysis set (FAS) is the primary analysis set for efficacy with an intention-to-treat (ITT) principle. In the FAS, all patients will be treated with at least one dose of the study drug and recorded with at least one clinical observation in the study. All subjects without any major protocol deviations will be involved in per-protocol set (PPS). The safety analysis will be conducted for randomized subjects who have completed at least one study visit and have safety data. Descriptive statistics will be performed on continuous variables, frequencies and categorical variables. All symptom duration, primary symptom duration, time to fever relief and time to fever clearance will be estimated by the Kaplan-Meier technique and be compared by the stratified log-rank test. Comparisons among groups will be conducted by an analysis of variance (ANOVA) and least significant difference*t*-test. In this multicenter trial, the Cochran-Mantel-Haenszel test, stratified by clinical centers, and the logistic regression model, adjusted for covariates, will be used. All data will be processed by a professional statistician using SAS 9.2 software (SAS, Cary, NC, USA), and a 2-sided *P*-value of < 0.05 is considered to be statistically significant.

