### Interventions

Gantong Granules and placebo are provided and manufactured by Beikelian Pharmaceutical & Technology Co., Ltd, Shenzhen, China. Considering the characteristics of Chinese herbal medicine, placebo is prepared by 10-fold dilution of 5 g of Gantong Granules and then condensed into granules. The minimum effective dose of Gantong Granules is 5 g. After 10-fold dilution, the placebo will not have any clinical or pharmacological effects. Placebo is almost identical to the test drug in appearance, smell and taste. This preparation of placebo has been used in herbal medicine trials in China and Japan. All drugs are concealed in uniform packages with the same labels and each package contains 5 plus 1 days’ dosage. Patients in the high-dose group, medium-dose group, low-dose group or placebo control group, will receive Gantong Granules 15 g, Gantong Granules 10 g plus placebo 5 g, Gantong Granules 5 g plus placebo 10 g or placebo 15 g, respectively. All drugs will be dissolved in 200 ml warm water and taken orally before each meal 3 times daily for 3 to 5 days. If all symptoms disappear within 3 days, the study drugs should be taken for just 3 days; if not, for 5 days. During the study, patients will be visited five times by the investigators. The follow-up visits last for 7 days after the treatment. Details of study procedures are shown in Figure 2.

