### Safety outcomes

Physical examination and some laboratory tests will be performed both before and after treatment for safety assessment. Physical examination includes temperature, respiration, blood pressure, heart rate and weight. Laboratory tests include routine blood test, urine analysis, liver function test (ALT, AST, ALP, STB, and γ-GT), renal function test (serum creatinine, microalbuminuria, and serum cystatin C), and electrocardiogram. Beyond that, before treatment, all subjects need to undergo a chest X-ray, and female patients of childbearing age need to take a urine pregnancy test.

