### Adverse event reporting

It is very important to ensure all patients’ safety during the trial. Adverse events (AEs) should be recorded in detail on the adverse event form (AEF). All patients experiencing an AE will be treated appropriately. Regarding a SAE, the investigator must record it on the SAE form, and it should be reported to the principal investigator, CFDA, ethics committees and the sponsor within 24 hours.

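### The safety set does not require a dose of study drug, so never-dosed patients can qualify, and its visit condition could exclude early reactors if it means a post-dose visit

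*Protocol article*

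**What the plan says.** The protocol article's Statistical analysis section states the safety population in one sentence: "The safety analysis will be conducted for randomized subjects who have completed at least one study visit and have safety data". That gives three conditions: randomization, one completed visit and safety data. Exposure is not among them.

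The same section does use an exposure condition for efficacy: "In the FAS, all patients will be treated with at least one dose of the study drug and recorded with at least one clinical observation".

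Four other sections bear on who meets the safety rule:

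- Safety outcomes: "Physical examination and some laboratory tests will be performed both before and after treatment for safety assessment". Some safety data therefore exist before any dose is taken.
- Interventions: "During the study, patients will be visited five times by the investigators". The text does not say which of these visits satisfies the safety rule.
- Adverse event reporting: "Adverse events (AEs) should be recorded in detail on the adverse event form (AEF". Serious events go on a separate form and are reported within 24 hours. Neither form is tied to a visit.
- Rejection criteria: these list patients who took no study medication, and also patients with nothing usable recorded post-dose. No analysis set is named.

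**The concern.** A safety set should contain the patients who were exposed to treatment and no others, because only they are at risk of a drug reaction. This rule replaces exposure with attendance and availability of data. Depending on how the visit condition is read, the set can be too wide (unexposed patients in the denominator) or too narrow (exposed patients missing from both numerator and denominator).

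Safety is a stated aim of this phase IIb trial, and its results are meant to inform the dose for phase III. With 60 patients per arm, adverse event counts will be low, and one patient more or less can change what a table appears to show.

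**Working it through.** **The only related figure in the plan.** The article gives no expected size for the safety set, so the arm size is the available denominator. It comes from the Sample size calculation section, where "the mean duration of all symptoms for the common cold was estimated to be 7 days with a standard deviation of 3 days" and the target difference is 2 days, "with 90% power and α = 0.05 (2-sided), the sample size needs to be 48 cases for each group". By the normal approximation, n = 2 × (1.960 + 1.282)² × 3² / 2² = 2 × 10.51 × 2.25 = 47.3, which rounds up to 48. With 20% drop-out, 48 / 0.80 = 60 per arm, and 4 × 60 = 240. The plan's figures reproduce and are not affected by this point.

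**The definitions side by side.**

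| Condition | Full analysis set | Safety set |
|---|---|---|
| At least one dose | required | not stated |
| Observation or data | one clinical observation | safety data, timing not stated |
| Visit | not stated | one completed visit, timing not stated |

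**Reading 1: a baseline visit counts.** A randomized, never-dosed patient with pre-treatment tests has a visit and safety data and qualifies. No dosed patient is lost through the visit condition. If k of 60 patients were never dosed and had no treatment-related event, the exposure-based rate is multiplied by (60 − k)/60. The values of k are assumptions:

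- k = 0: factor 1.00
- k = 3: 57/60 = 0.95; for example, 6 events give 6/57 = 10.5% by exposure and 6/60 = 10.0% by the stated rule
- k = 6: 54/60 = 0.90; 6 events give 6/54 = 11.1% against 6/60 = 10.0%

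**Reading 2: a visit after dosing is needed.** A patient who takes a dose, reacts and leaves before that visit fails the condition, even with a completed form. Take an arm of 60, all dosed, with 6 reactors (assumed), of whom y leave too early. The rate becomes (6 − y)/(60 − y):

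- y = 0: 6/60 = 10.0%
- y = 1: 5/59 = 8.5%
- y = 3: 3/57 = 5.3%

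With only 3 reactors and one lost, 3/60 = 5.0% becomes 2/59 = 3.4%. A never-dosed patient who attends the later visit would still be counted under this reading.

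**Effect of the Rejection criteria.** If they apply to the safety set, never-dosed patients leave, but so do dosed patients with no usable post-dose record. If they do not apply, never-dosed patients can stay. Neither case makes exposure alone the test for membership.

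**The case against.** The strongest reply is that, read naturally, the documents come close to the right set. Eligibility already needs a clinical diagnosis, blood and urine tests and a chest X-ray, so every randomized patient has been assessed before treatment and that visit satisfies the rule. The Rejection criteria then take out the never-dosed. What remains is approximately the treated population. Any further detail could be in the statistical analysis plan, which the Data management section places at blind review.

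Much of this stands, and it rules out three stronger conclusions that a reader might draw.

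- *That the rule loses serious early reactions.* This happens only if the visit must follow dosing, and the text does not say so.
- *That the Withdrawal criteria take patients with anaphylaxis or serious events out of the safety analysis.* They end participation and say nothing about discarding data. Such patients would have an adverse event or serious adverse event form.
- *That the Rejection criteria contradict the safety rule.* They name no analysis set. The two sections are left unreconciled, not in conflict.

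It is also fair that, under double blinding, there is no stated reason for the never-dosed fraction to differ between arms. Similar dilution in every arm leaves rate ratios largely unchanged.

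What does not stand is the idea that this is only detail left to a later document. The article states a specific rule and omits exposure from it, although it requires exposure for the full analysis set in the same section. Relying on the Rejection criteria to repair the omission would also bring in their exclusion of dosed patients without usable records.

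**Conclusion.** The point holds in limited form. The safety set is badly specified: as worded it can admit randomized patients who were never exposed, and on one possible but unstated reading of the visit condition it could leave out exposed patients who reacted and left early. The link to the Rejection criteria is not settled.

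The size cannot be computed, because the documents give no number of never-dosed or early-leaving patients. It is probably small. An assumed 3 in 60 never dosed changes a rate by a factor of 0.95, for example from 10.5% to 10.0%. The larger shifts, such as 5.0% to 3.4%, need both the post-dose reading and the loss of a reactor before that visit. They are illustrations, not predictions.

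The definition should be corrected because doing so is easy and because event counts in arms of 60 are sensitive to single patients. It is not evidence that the safety results will be seriously biased.

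**What to change.** Replace the safety-set sentence with a definition based on exposure:

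- The set is all randomized patients who took at least one dose of study drug, analysed by treatment actually received, with no condition on visits.
- All adverse events recorded on the adverse event and serious adverse event forms are counted, whether or not the patient attended a later visit. The patient diary is described only for symptoms and temperature, so it should not be presumed to be a source of adverse events.
- The Rejection criteria do not remove dosed patients from this set.

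Laboratory and ECG summaries can still use the patients with a post-treatment result. It is the adverse event denominator that must rest on exposure.

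The cost is a few lines in the protocol or the statistical analysis plan. No extra visits or data are needed, because dosing and both event forms are already part of the trial's records. The article reports that recruitment is still under way and that the analysis plan is settled at blind review before the data are locked, so the change can be made without knowledge of treatment allocation.

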### Recruitment

We plan to recruit patients through advertisements and recommendations. A total of 240 patients will be recruited in this trial at the following 5 hospitals across China: 1) West China Hospital of Sichuan University, 2) the Affiliated Hospital of Chengdu University of TCM, 3) The First Hospital of Hunan University of TCM, 4) the Affiliated Hospital of Nanjing University of TCM, 5) the Affiliated Hospital of Jangxi University of TCM. Forty-eight patients will be recruited at each center.

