### Randomization and blinding

Using a stratified block randomization method, 240 eligible patients will be randomly allocated to the high-dose group, medium-dose group, low-dose group or placebo control group in a 1:1:1:1 ratio. The randomization sequence will be generated using the PRCO PLAN function of the analysis system of SAS software (SAS, Cary, NC, USA). The randomization lists will be concealed in a lightproof sealed envelope. The sealed envelopes will be kept by the leader and the sponsor of the study. Treatment allocation will be blinded to the participants and investigators throughout the course of the study. The emergency envelope will be saved in each center, and only be opened for medical emergency purposes.

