#### Secondary outcomes

Secondary outcomes include duration of primary symptoms and each symptom, time to fever relief and time to fever clearance, change in TCM symptom score, and change in Symptom and Sign Score.

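### The ANOVA and LSD comparisons of the secondary score outcomes state no centre term; if centres differ, these tests are slightly conservative

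*Protocol article*

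**What the plan says.** In the protocol article, the Statistical analysis section goes through the methods in turn:

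- Four time outcomes (all-symptom duration, primary-symptom duration, fever relief, fever clearance) are estimated by Kaplan-Meier and will "be compared by the stratified log-rank test". The stratum is not named.
- "Comparisons among groups will be conducted by an analysis of variance (ANOVA) and least significant difference" t-test. Neither the outcomes covered nor the model terms are given.
- For the multicentre setting, "the Cochran-Mantel-Haenszel test, stratified by clinical centers, and the logistic regression model, adjusted for covariates, will be used".

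The secondary outcomes include "change in TCM symptom score, and change in Symptom and Sign Score", which later sections define as percentage reductions from baseline (PSSR and PSSSR).

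On design, the Randomization and blinding section says "Using a stratified block randomization method, 240 eligible patients will be randomly allocated", without naming the stratification factor. The four arms (three doses and placebo) are of equal size. The Recruitment section says "Forty-eight patients will be recruited at each center", at five hospitals.

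**The concern.** The section names centre for one test and stratification for another. Between them it leaves a comparison of arm means with no adjustment stated. The centre-stratified Cochran-Mantel-Haenszel test does not fill the gap: it serves categorical data, and no efficacy outcome listed in the article is categorical. The two continuous score outcomes therefore fall to the ANOVA and LSD t-test.

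When allocation is balanced within centre, centre differences drop out of the arm contrasts. A model without centre nevertheless counts them as error. The standard error is then larger than the true sampling variability of the contrast, intervals are too wide, and the test rejects less often than its nominal level. The trial aims to find a dose-effect relationship and inform phase III dose selection, so precision in the pairwise contrasts has some value. What is at stake is modest efficiency on secondary outcomes, and only if centres differ.

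**Working it through.** **The plan's own figures.** With a difference of 2 days, SD 3 days, two-sided 5% and 90% power, n per arm = 2 × (1.960 + 1.282)² × 3² / 2² = 47.3, rounded up to 48. Then 48 / 0.80 = 60 per arm, and 4 × 60 = 240 = 5 × 48. The stated sample size reproduces. It concerns the primary outcome, and this point does not touch it.

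**Layout.** 48 per centre at 1:1:1:1 gives 12 per arm per centre, if centre is the stratum and allocation is balanced. Error degrees of freedom are 240 − 4 = 236 without centre and 236 − 4 = 232 with it.

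**Assumptions.** The article gives no ICC, score SD or score effect. Set the total variance to 1, with between-centre variance ICC and within-centre variance 1 − ICC. Take ICC = 0, 0.05, 0.10 and 0.20, a difference of 0.5 total SD, and all 240 patients analysed.

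**Standard error.** In the balanced layout the arm difference has variance (1 − ICC) × 2/60. The expected error mean squares are:

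- with centre: 1 − ICC
- without centre: [232(1 − ICC) + 4((1 − ICC) + 48 ICC)] / 236 = (1 − ICC) + ICC × 192/236

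The standard error overstatement is the square root of their ratio, minus 1:

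- ICC 0: none
- ICC 0.05: √(0.9907/0.95) = 1.021, so 2.1%
- ICC 0.10: √(0.9814/0.90) = 1.044, so 4.4%
- ICC 0.20: √(0.9627/0.80) = 1.097, so 9.7%

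**Level and power.** Simulation of 5 centres × 4 arms × 12 patients, 20,000 runs per setting, pairwise t-test at nominal two-sided 5%:

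| ICC | Level without centre | Level with centre | Power without centre | Power with centre | Difference (points) |
|---|---|---|---|---|---|
| 0 | 4.9% | 4.9% | 77.5% | 77.5% | 0 |
| 0.05 | 4.7% | 5.2% | 79.2% | 80.5% | 1.3 |
| 0.10 | 3.7% | 4.6% | 79.7% | 82.0% | 2.4 |
| 0.20 | 3.3% | 5.0% | 81.3% | 85.9% | 4.5 |

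Monte Carlo error on the level is about √(0.05 × 0.95 / 20,000) = 0.15 points. Both power columns rise with the ICC because the total SD is held fixed, so a larger centre share leaves less within-centre noise. The loss is the gap between the columns. An analytic approximation gives gaps of 1.4, 2.9 and 5.7 points. It sets the no-centre error variance at the full total variance, which is slightly too high for five centres, so these are upper figures.

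**The case against.** The strongest reply is that the article does not specify an ANOVA without centre. It names a family of methods, and an ANOVA with a centre factor is still an ANOVA. Analysis is to follow a statistical analysis plan that is not shown, and model terms are ordinary content for such a plan. This stands in part. A reader might infer that centre is deliberately excluded, and the text does not support that. It does, however, name an LSD comparison of arm means and state adjustment only for the methods around it, so anyone following it literally would omit centre. Adding centre is a better method at almost no cost, whatever the unseen plan says.

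Two links are inferred. Centre is not named as the randomisation stratum, although equal numbers per centre and the centre-stratified Cochran-Mantel-Haenszel test point to it. PSSR and PSSSR are not expressly assigned to the ANOVA, although the main durations are assigned elsewhere.

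The size is also easy to overstate. The shortcut 1/√(1 − ICC) gives 2.6%, 5.4% and 11.8%, which is too high for only five centres. Both outcomes are percentage reductions from the patient's own baseline, so a constant proportional difference in grading between hospitals cancels. That is a reason to expect the ICC to be at the lower end. A reader might further infer that power is certainly lost, that false positives are inflated, or that the main conclusion is at risk. None of these follows: the loss is zero if centres do not differ, the error is conservative, and the primary outcome has a stratified log-rank test.

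**Conclusion.** The point holds as a minor, conditional one. As written, the comparisons that most naturally cover PSSR and PSSSR carry no stated centre term, while neighbouring tests are stratified. If centres differ, standard errors are overstated by about 2%, 4% and 10% at ICCs of 0.05, 0.10 and 0.20, and power at 0.5 SD is lower by about 1, 2 to 3, and 5 points. At an ICC of 0 there is no loss. These figures rest on an assumed ICC and effect size, centre as the stratum, 12 patients per arm per centre, and complete data. Treatment estimates remain unbiased under the balanced allocation. The primary outcome and the 48/60/240 sample size are unaffected.

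**What to change.** In the Statistical analysis section, or in the statistical analysis plan before database lock, state that PSSR and PSSSR will be analysed with a linear model containing treatment arm and centre, plus any other factor used to stratify randomisation. Take the pairwise arm differences and their confidence intervals from that model. Name the randomisation stratum in the same edit, so that the adjustment can be seen to match the design.

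The cost is one sentence and 4 of 236 degrees of freedom, with no new data and no more patients. If centres turn out not to differ, simulated power is 77.5% with or without the term.

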## Discussion

The common cold is something that one may experience multiple times throughout his or her lifetime. To date, however, there is no well-proven treatment or cure for this disease. It is widely recognized that the randomized controlled trial is a ‘gold standard’ methodology for evaluating the clinical efficacy and safety of an intervention. Although Chinese herbs have been widely used to treat the common cold in China and many other countries, the quality of most prior studies was assessed to be generally low due to methodological limitations like inadequate randomization, lack of double blinding, non-placebo control, incomplete outcome data, and so on [21,22]. So, there is a lack of robust evidence to support the clinical utility of TCM treatment.

For the above reasons, this protocol is rigorously-designed in accordance with the CONSORT (Consolidated Standards of Reporting Trials) statement and SPIRIT (Standard Protocol Items: Recommendations for Interventional Trials) statement [23,24]. As far as we know, this study will be the first multicenter, double-blind, placebo-controlled and randomized clinical trial that is designed to treat CCWHS. Based on scientific and objective assessment, this study will provide high-quality evidence on the efficacy and safety of Gantong Granules in treating CCWHS, and may help to optimize the dose selection for a phase III clinical trial.

